#### Placebo group

In order to evaluate the absolute efficacy and safety of Qingpeng ointment for AGA and reduce the risk of bias, we chose placebo as comparison. Participants in control group will be treated with placebo ointment (produced by Tibet Cheezheng Tibetan Medicine Co., Ltd). The ingredients of placebo ointment include purified water, liquid paraffin, glycerinum, methylparaben, and food coloring. The placebo ointment is the same as Qingpeng ointment in texture, color, smell, and packaging. The usage of placebo ointment is the same as Qingpeng ointment.

#### Rescue medicine

DSSRT (produced by Beijing Novartis Pharmaceutical Co., Ltd; specification: 75mg/tablet, 10 tablets/box) will be given to participants in both treatment group and control group as rescue medicine. Patients in both groups are recommended to take the rescue medicine only when the VAS score of joint pain is ≥ 7 points (scale of 0 to 10), which is scored by patients themselves. Patients will also be recommended not to take the rescue medicine when joint pain is reduced to a tolerable extent (VAS score reduce to less than 7 points). The recommended dose is one tablet per time, once daily, and the maximum dose is one tablet per time, twice a day.

### Assignment of interventions

#### Randomization

Participants will be randomly assigned to treatment group and control group at a ratio of 1:1, with 103 cases in each group. The random sequence was generated by an independent statistician, using the SAS 9.2 software.

#### Allocation concealment and blinding

Sequentially numbered drug containers of identical appearance were used to achieve allocation concealment. Two hundred and six drug boxes with identical appearance were numbered as 001–206. According to the random sequence, Qingpeng ointment and placebo ointment were put into the corresponding numbered boxes, with three tubes of Qingpeng ointment or placebo ointment in each box. One box of DSSRT was also put into each drug box at the same time. Special personnel are assigned to manage the study drugs in each hospital, and the corresponding sequence of drugs will be distributed to each patient according to their recruitment sequence. Throughout the study, the investigators and the participants will not know which group the participants are assigned to. For each participant sequence, a corresponding emergency letter was made, which records the allocation result of that participant. When a participant experience serious adverse events and the allocation result needs to be known, investigators can open the emergency letter. The process of unblinding, including reasons, time, and treatment results, should be recorded on the case report form.

### Outcomes

#### Primary outcomes

Because the objective of this study is to investigate the efficacy of Qingpeng ointment for relieving pain and swelling of joints in patients with AGA, changes in joint pain severity (measured using VAS), joint swelling degree (measured using VAS), and width and thickness of affected joints (measured using vernier calipers) between baseline and treatment completion will be considered as the primary outcomes.Joint pain: Degree of joint pain will be measured by participants, using a visual analogue scale (VAS, 0–10 points, 0=no pain, 10=intolerable pain), at baseline, every day during treatment, and after 7-day treatment.Joint swelling:2.1 The width and thickness of each affected joint will be measured using vernier calipers (brand: Ruineng, model: NR0139) at baseline, every day during treatment, and after 7-day treatment.2.2 Degree of joint swelling will be measured by participants, using a visual analogue scale (VAS, 0–10 points, 0=no swelling, 10=intolerable swelling), at baseline, every day during treatment, and after 7-day treatment.

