### Sample size estimation

This study includes two primary outcomes: joint pain and joint swelling. Sample size was estimated based on these two primary outcome measures. Estimation according to joint pain was based on results from a previous study [23]. In this study, 47% participants in treatment group (Qingpeng ointment plus diclofenac sodium tablets) had significant relief of joint pain (the score of joint pain degree measured by a self-developed scale reduced by 6 points), and 25% participants in control group (diclofenac sodium tablets) had significant relief of joint pain. On the basis of a 5% type I error rate (*α*=0.05) and a power of 90% (*β*=0.1), the sample size of each group was 82. Assuming a 20% dropout rate, a total of 206 participants should be recruited, with 103 participants in each group.

Estimation according to joint swelling was likewise based on results from another previous study [19], which established score of joint swelling measured by a 0–3 points scale as 0.45 points after receiving Qingpeng ointment plus etoricoxib tablets, and the estimated standard deviation is 0.37. Score of joint swelling after receiving vaseline plus etoricoxib tablets is 0.87, and the estimated standard deviation is 0.64. On the basis of a 5% type I error rate (*α*=0.05) and a power of 90% (*β*=0.1), the sample size of each group was 27. Assuming a 20% dropout rate, a total of 68 participants should be recruited, with 34 participants in each group.

Based on these results, we chose the larger sample size of 206 participants, with 103 participants in each group.

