### Statistical analysis

Statistical analysis will be performed using SAS 9.2 software, with a statistical significance of *p* value less than 0.05. Normally distributed continuous variables will be described using mean ± standard deviation (SD), and non-normally distributed continuous variables will be described using median and interquartile range (IQR). Categorical variables will be described using frequencies and percentages. Primary outcomes will be analyzed according to the intention-to-treat principle. Intra-group differences of continuous variables will be tested for significance using paired-samples *t* test when the data is normally distributed, and will be tested using non-parametric test when the data is non-normally distributed. Between-group differences of continuous variables will be tested for significance using independent-samples *t* test when the data of the two groups are normally distributed and have equal variance, and will be tested using non-parametric test when the data of the two groups are non-normally distributed or have unequal variances. Chi-square test will be used for categorical data. Data from participants who drop out from this study will be implemented by the last-observation-carried-forward (LOCF) method. Interim analyses will not be performed. For the co-primary endpoints, Bonferroni correction will be performed to correct multiplicity.

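### The primary family is listed as three or four measures but counted as two, so the planned Bonferroni correction has no fixed divisor and would not hold 5% if two were used

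*Protocol article*

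**What the plan says.** All references are to the protocol article, under Methods.

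- **Primary outcomes.** Alongside change in pain VAS, the section lists "joint swelling degree (measured using VAS), and width and thickness of affected joints (measured using vernier calipers", and says that the changes "between baseline and treatment completion will be considered as the primary outcomes". Its numbered list has joint pain as item 1 and joint swelling as item 2. Swelling is split into 2.1 (calipers) and 2.2 (VAS). On the calipers it adds: "The width and thickness of each affected joint will be measured using vernier calipers".
- **Sample size estimation.** "This study includes two primary outcomes: joint pain and joint swelling". Pain and swelling are each sized separately: "On the basis of a 5% type I error rate". The swelling calculation uses a 0–3 point score, which is none of the three swelling measures in the outcomes list.
- **Statistical analysis.** "For the co-primary endpoints, Bonferroni correction will be performed to correct multiplicity". No number of tests is given.

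The Discussion keeps both descriptions. It names pain and swelling as the primary outcomes and then describes swelling as measured in two ways.

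**The concern.** A Bonferroni correction is defined by its divisor. The only explicit count in the article is two, but the list of primary variables is longer, and nothing says how swelling VAS, width and thickness become a single swelling test. Because calipers are used on every affected joint, a patient may also contribute several widths and thicknesses.

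If the divisor is two and every listed variable is tested, swelling gets two or three chances at 0.025 and pain gets one, and the total exceeds 5%. The result can turn on which section the analyst follows. A trial in which only thickness reaches p = 0.02 is positive with a divisor of two (0.025) and negative with a divisor of three (0.0167) or four (0.0125). If this is left open, the choice can be made after the results are known.

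**Working it through.** **1. The plan's own figures.** The inputs are in Sample size estimation: pain relief 47% against 25%; swelling 0.45 (SD 0.37) against 0.87 (SD 0.64); alpha 0.05; power 90%; dropout 20%.

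- Pain: n = [z_α√(2·0.36·0.64) + 1.2816·√(0.47·0.53 + 0.25·0.75)]² / 0.22². One-sided (z_α = 1.6449) this gives 79.6, so 80, against 82 stated. Two-sided it gives 98.
- Swelling: n = (0.37² + 0.64²)(z_α + 1.2816)² / 0.42². One-sided this gives 26.5, so 27, as stated. Two-sided it gives 33.
- Dropout: 82/0.8 = 102.5, so 103, and 27/0.8 = 33.75, so 34, both as stated.

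The stated sizes are therefore met, or nearly met, only with an undivided 5%. The sizing makes no allowance for any divisor, so it does not show which one was intended. Sidedness is a separate matter.

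**2. Number of tests.** Pain VAS, swelling VAS and calipers as one item give three. Splitting width from thickness gives four. Testing joints separately would add more, and this is not quantified here.

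**3. Family-wise error if any one success counts.** For independent tests it is 1 − (1 − a)^m, where m is the number of tests and a the level of each.

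| Tests m | Level of each | Error if independent | Sum of levels (upper bound) |
|---|---|---|---|
| 2 | 0.025 | 4.94% | 5.0% |
| 3 | 0.025 | 7.31% | 7.5% |
| 4 | 0.025 | 9.63% | 10.0% |
| 3 | 0.0167 | 4.92% | 5.0% |
| 4 | 0.0125 | 4.91% | 5.0% |

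For two-sided tests on jointly normal statistics, independence gives the largest value (Šidák's inequality).

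**4. Correlated measures.** The article gives no correlations, so a common correlation is assumed and varied. These are simulated results, two-sided, each test at 0.025, with 2 million draws.

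| Correlation | Three tests | Four tests |
|---|---|---|
| 0.3 | 7.0% | 9.1% |
| 0.5 | 6.5% | 8.3% |
| 0.7 | 5.7% | 6.9% |
| 0.9 | 4.4% | 4.9% |

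With pain independent and the three swelling variables correlated at 0.5 or 0.7, four tests give 8.9% or 8.1%.

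**5. Power cost of a larger divisor.** Two-sided power is Φ{[0.22√n − z√0.4608]/√0.4366}, where 0.4608 = 2·0.36·0.64 and 0.4366 = 0.47·0.53 + 0.25·0.75.

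- n = 82, level 0.025 (z = 2.2414): (1.9922 − 1.5215)/0.6608 = 0.712, so 76%.
- n = 82, level 0.0125 (z = 2.4977): (1.9922 − 1.6955)/0.6608 = 0.449, so 67%.
- For three tests (0.0167) the figure is 71%.
- With all 103 per group, 0.025 gives 86% and 0.0125 gives 79%.

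These use the binary relief rates in the sizing section, not the VAS change that is the listed outcome, so they only illustrate the cost.

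**The case against.** The strongest reply is that this is a hierarchy and not a conflict. There are two domains, pain and swelling, and the numbered list nests the swelling measures under one heading. The divisor and the rule for swelling could sit in an analysis plan that is not shown, and a journal article need not carry them. Much of this stands. The missing divisor alone would not be a finding, and the article's own numbering supports three measures as well as four. What remains is that the outcomes section calls each measure primary while the sizing section counts two. An analysis plan that fixes a divisor for separate tests of the listed measures must depart from one of those sections.

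A reader might infer that the plan runs at nearly 10% error. The article does not support that. It never states a divisor of two, and 9.6% needs that divisor, four separate tests, success on any one, and independence. Independence is implausible for three measures of swelling in the same joints.

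A reader might also infer two opposed success rules, because co-primary strictly means that all must succeed and would then need no correction. The article does not adopt that meaning. Planning a Bonferroni correction points to success on any one, so this is loose terminology.

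**Conclusion.** The mismatch in the count of primary outcomes is real and should be fixed. The inflation is conditional. It arises if the divisor is two, each listed measure is tested separately, and any one success counts. On those terms the family-wise error is at most 7.3% for three tests or 9.6% for four, and about 6% to 9% at assumed correlations of 0.3 to 0.7. It disappears near a correlation of 0.9. A divisor equal to the number of tests keeps it at or below 5% whatever the correlation. The defect is therefore an unfixed primary family, with possible inflation and not planned inflation. Confidence is high on the mismatch and lower on the size of the error.

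**What to change.** Before unblinding, make Primary outcomes, Sample size estimation and Statistical analysis agree on one family. There are two ways:

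1. **Two primaries:** pain VAS plus one named swelling measure, with the other swelling measures secondary.
2. **All listed measures primary:** each reduced to one value per patient by a stated rule for patients with several affected joints, with the number of tests (three or four) written out.

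In either case, apply Holm or Bonferroni over exactly that number and state that success on any one counts. Holm is never less powerful than Bonferroni on the same family.

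The change is to wording only and needs no new patients or measurements. Option 1 gives up a confirmatory claim on the other swelling measures. Option 2 tightens the first-step threshold for pain as well as swelling. For four tests it is 0.0125, and illustrative pain power at 82 per group falls from about 76% to 67%.

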#### Treatment period

Patients in the treatment group will be treated with Qingpeng ointment, and patients in the control group will be treated with placebo ointment. Patients in both groups will be given diclofenac sodium sustained-release tablets (DSSRT) as rescue medicine. Drugs for other underlying diseases such as antihypertensive drugs, hypoglycemic drugs, and hypolipidemic drugs are permitted to be taken during the treatment period. And other Chinese patent medicine are prohibited during the trial. When participants experience severe skin allergies at application site, or experience serious adverse events, investigators will advise them to discontinue using the study drug. The degree of joint pain, swelling, redness, and mobility will be scored and recorded on patient diary every day by patients, and the width and thickness of affected joints will also be measured and recorded every day by themselves. The course of treatment is seven days.

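### Pain and swelling VAS are recorded daily, but the stated primary analysis is an unadjusted baseline-to-completion comparison with LOCF; a baseline-adjusted repeated-measures model would serve the same primary contrast better.

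*Protocol article*

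**What the plan says.** Primary outcomes (protocol article) lists pain VAS, swelling VAS and caliper width and thickness. It defines the endpoint as a change: "between baseline and treatment completion will be considered as the primary outcomes". For both VAS it gives the measurement times as "at baseline, every day during treatment, and after 7-day treatment". Treatment period confirms that the daily values are patient diary entries: "The degree of joint pain, swelling, redness, and mobility will be scored and recorded on patient diary every day by patients".

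Statistical analysis then names the comparison: "Between-group differences of continuous variables will be tested for significance using independent-samples" t test, with a non-parametric test if the data are non-normal or the variances unequal. It names no covariate and no repeated-measures method. On dropout it says: "Data from participants who drop out from this study will be implemented by the last-observation-carried-forward (LOCF) method". Bonferroni correction is planned across the co-primary endpoints.

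**The concern.** Seven daily scores per patient are collected for each VAS, and the stated between-group test uses two time points. Two losses follow.

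- **Baseline.** A change score fixes the weight on baseline at one. Unless the true regression slope is one, that leaves avoidable variance in the comparison.
- **Daily course.** For a patient who stops on day 3, the diary contributes only a day-3 value treated as the treatment-completion value, although a flare is expected to move over those days. Sample size estimation allows for 20% dropout, so this could affect a fair share of patients.

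There is also a question of what the trial can show. The objective is relief of pain and swelling in an acute flare. If both groups approach zero by day 7, faster relief in the first days will not appear in a completion-only comparison.

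**Working it through.** **The plan's own figures.** With 47% v 25% pain response, mean proportion 0.36, 5% alpha and 90% power:

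- n = 2 × 0.36 × 0.64 × (1.645 + 1.282)² / 0.22² = 81.5, so 82 per group; 82/0.8 = 102.5, so 103.
- Swelling: mean variance (0.37² + 0.64²)/2 = 0.273, difference 0.42, giving 26.5, so 27; 27/0.8 = 33.75, so 34.

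Both match the article, with a one-sided normal quantile (a separate matter). Neither uses the SD of a VAS change, a between-day correlation or the daily scores. The article therefore offers no direct input for what follows, and every correlation below is an assumption.

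**Step 1: baseline adjustment with day 7 as the target.** Day 7 here means the treatment-completion reading. Take equal SDs (set to 1) and correlation r between baseline and day 7.

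- Variance of the change score: 2(1 − r).
- Variance after baseline adjustment: 1 − r².
- Ratio: (1 + r)/2.

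| r | change | adjusted | ratio |
|---|---|---|---|
| 0.5 | 1.00 | 0.75 | 0.75 |
| 0.7 | 0.60 | 0.51 | 0.85 |
| 0.8 | 0.40 | 0.36 | 0.90 |

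If the day-7 SD is k times the baseline SD, the ratio is k²(1 − r²)/(1 + k² − 2rk), which falls as k falls. At r = 0.5 and k = 0.5 it is 0.1875/0.75 = 0.25. Shrinking SDs therefore strengthen this step. With complete data, modelling the daily scores adds essentially nothing to the day-7 contrast beyond baseline adjustment. Their value there is for patients with missing day-7 scores.

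**Step 2: the average over days 1 to 7, equal daily SDs.** Variance relative to the baseline-adjusted day-7 score:

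- Common correlation r: [(1 + 6r)/7 − r²]/(1 − r²). For r = 0.5, 0.7 and 0.8 this is 0.43, 0.50 and 0.52.
- AR(1), lag-1 correlation 0.6 to 0.9: 0.38 to 0.46.
- On plain change scores, as the plan would compute them: 0.57 under common correlation and 0.42 to 0.54 under AR(1) with 0.5 to 0.95.

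The SE of the change-score version falls by about 24% (1 − √0.57) to 35% (1 − √0.42).

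**Step 3: let the SD fall with the mean.** Take exponential decline from VAS 6, with half-lives 2 v 3, 1.5 v 2 and 3 v 4 days, and the correlations of Step 2 (common 0.5 to 0.8, AR(1) 0.6 to 0.9). The day-7 effects are 0.66, 0.29 and 0.59 points; the 7-day average effects are 0.76, 0.48 and 0.54.

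| daily SD | variance ratio, average v day 7 | efficiency of average (effect ratio² / variance ratio) |
|---|---|---|
| proportional to √mean | 0.70 to 2.00 | 0.83 to 1.98 |
| proportional to mean | 1.4 to 10.4 | 0.26 to 0.59 |

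The only SDs in the article, for swelling on a 0 to 3 scale, are 0.37 at mean 0.45 and 0.64 at mean 0.87. The smaller mean has the smaller SD.

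**Step 4: shape of the effect.** Even with equal SDs, the change-score average gains power only if its effect exceeds √0.57 = 0.76 of the day-7 effect (about 0.65 under the most favourable AR(1)). An effect growing linearly from day 1 to day 7 averages 4/7 = 0.57 of its day-7 size. Where day 7 has 90% power, the average then has about 69% to 81%.

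**Step 5: floor.** The VAS stops at 0, entry is allowed at 3, and onset may be up to 1 week before the visit, so completion can fall about 14 days after onset. The cited treated-arm swelling mean is 0.45/0.37 = 1.2 SD above zero. No day-7 VAS distribution is given, so the proportion at the floor cannot be computed.

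**The case against.** The strongest reply is that nothing here is wrong or contradictory. Change at the end of a 7-day course is a legitimate target that fits the stated objective, and supporting longitudinal analyses and covariates are ordinary content for an analysis plan that is not shown. Much of this stands. It is why the day-7 contrast stays primary, and why the absence of supporting analyses is not held against the article. It does not cover the primary test and the missing-data rule, which the article itself states.

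A reader might infer that the plan throws away half its precision, or that using the daily mean would be worth 1.9 to 2.6 times as many patients. The documents do not support this. Those figures need equal daily SDs and the same effect in both contrasts. The first assumption sits badly with the floor argument itself, since scores crowding towards zero imply a shrinking SD. Under that pattern the average can lose (Step 3).

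A reader might also infer that the floor at day 7 is established. It is plausible, but 14 days from onset and 3 points left to gain are the extremes of eligibility, not the expected patient.

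Finally, the average answers a different question. It includes the early days, when pain of VAS 7 or more, and so rescue diclofenac, is more likely. That stands as a cost.

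**Conclusion.** The concern holds as a moderate, inexpensive improvement to the stated analysis. For the pain and swelling VAS, the planned comparison leaves baseline unadjusted and uses diary data only through LOCF. With equal SDs and r of 0.5 to 0.8, adjustment brings the day-7 variance to 0.75 to 0.90 of the change-score value, and lower if day-7 scores are less variable than baseline. A repeated-measures model also lets dropouts contribute their observed course, under a missing-at-random assumption, in place of a carried value.

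The 7-day average is worth reporting because it can show early relief that day 7 may miss. Its precision advantage depends on variances and an effect shape that the article does not give, so it should not displace the primary on those grounds.

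**What to change.** For the pain and swelling VAS, before unblinding:

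1. Replace the change-score t or rank test and LOCF with a baseline-adjusted repeated-measures model on all daily scores, with treatment by day effects.
2. Keep the day-7 (treatment-completion) difference as the primary contrast, within the planned Bonferroni correction. State whether it is the last diary entry or the visit score.
3. Name the average difference over days 1 to 7 as a key secondary, and describe it as a separate question about the whole treatment week.
4. Optionally add days since onset as a covariate; the 1-week eligibility limit means it has to be established for every patient.

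The cost is analysis wording and standard mixed-model code, with no new visits or data. The downsides are one extra pre-specified contrast, the need to monitor diary completeness, and an average that takes in the days when rescue use is more likely.

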To the best of our knowledge, this study is the first multi-center, randomized, double-blind, and placebo-controlled clinical trial to assess the efficacy of Qingpeng ointment for AGA. In terms of outcome selection, considering from the perspective of patients, we chose joint pain and joint swelling as primary outcomes, and joint mobility, joint redness, remaining amount of rescue medicine, C-reactive protein, and serum uric acid as secondary outcomes. Different from previous studies, for the primary outcome of joint swelling, we will use vernier calipers to measure the width and thickness of affected joints, and evaluate the relief of joint swelling using the change of width and thickness. We will also use the visual analogue scale to measure the degree of joint swelling. Measuring joint swelling in these two ways is an innovation different from previous studies. Moreover, the intervention and control of this study are only Qingpeng ointment and placebo ointment. Therefore, in order to improve the compliance of participants, we chose DSSRT as a rescue medicine. Participants in both treatment group and control group can take rescue medicine when the VAS score of joint pain is ≥ 7 points, to relieve the pain. In this way, the compliance of participants can be improved, and the dropout rate of this study can be reduced. After the treatment period, the remaining amount of Qingpeng ointment/placebo ointment will be recorded to assess the compliance of participants to the treatment regimen, and the remaining amount of rescue medicine will also be used as a secondary outcome for evaluating the efficacy of Qingpeng ointment.

The limitation of this study is that the only intervention and control drug are Qingpeng ointment and placebo ointment. Patients with AGA may experience very severe joint pain. The compliance of participants may be affected, if only externally applied drugs are given. In order to improve the compliance of participants, DSSRT will be used as rescue medicine. The investigators will also explain the study protocol and medication requirements to participants detailedly, to ensure that the participants fully understand how to use the drugs. During the treatment period, participants will be instructed regularly to apply the drug on time, and come back to hospital for follow-up.

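### The caliper co-primary is a plain change in joint dimensions at any joint site, compared without adjustment for baseline dimension or site; adjusting for both protects power at almost no cost

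*Protocol article*

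**What the plan says.** Under Primary outcomes, the protocol article counts among its primary outcomes the change in "width and thickness of affected joints (measured using vernier calipers) between baseline and treatment completion". It adds that "The width and thickness of each affected joint will be measured using vernier calipers". The Discussion says the trial will "evaluate the relief of joint swelling using the change of width and thickness". Neither place expresses the change relative to the joint's own size or to an unaffected joint.

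The inclusion and exclusion criteria name no joint site and no index joint. Under Randomization: "Participants will be randomly assigned to treatment group and control group at a ratio of 1:1, with 103 cases in each group". No balancing on joint site is described.

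Under Statistical analysis: "Between-group differences of continuous variables will be tested for significance using independent-samples" t test, or a non-parametric test where the data are non-normal or the variances unequal. No covariate is named.

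Sample size estimation covers pain responders and a 0-3 swelling score. It gives no effect, SD or important difference for the caliper measurement.

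**The concern.** An affected joint may be small or large. If a swollen joint loses a roughly constant fraction of its size as it settles, a partly improved large joint can lose more millimetres than a fully recovered small one. The spread of change then reflects which joint was affected as well as how well the patient did. An unadjusted comparison leaves all of that spread in its error term, although baseline dimension, which would explain much of it, is measured anyway.

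Two things are at stake. One is power on the only primary outcome that is not a self-rated VAS score. The other is the reading of the result, because a pooled millimetre difference does not translate into a degree of relief at any particular joint.

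**Working it through.** **1. The plan's own figures.** For pain the inputs are "47% participants in treatment group", "25% participants in control group", "a 5% type I error rate" and 90% power. With mean proportion 0.36,

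n = [z(α)·√(2·0.36·0.64) + 1.282·√(0.47·0.53 + 0.25·0.75)]² / 0.22².

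One-sided (z = 1.645): (1.117 + 0.847)² / 0.0484 ≈ 80, within two of the stated 82. Two-sided (z = 1.960): 98. Dropout: 82/0.8 = 102.5, so 103 as stated. For the 0-3 swelling score, a difference of 0.42 and SD √[(0.37² + 0.64²)/2] = 0.523 give 27 one-sided, as stated, and 33 two-sided. None of these figures concerns the calipers. Here 82 serves only as the evaluable number per arm.

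**2. Where the extra variance comes from (all inputs assumed).** One joint per patient. Small, medium and large joints of 30, 70 and 100 mm in a 60/25/15% mix. Mean shrinkage 6% of size (control) v 10% (treated), SD 5% of size, measurement error SD 1 mm.

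- Mean size: 0.60·30 + 0.25·70 + 0.15·100 = 50.5 mm. Mean changes: 3.03 and 5.05 mm, difference 2.02 mm.
- Variance of size: 0.60·20.5² + 0.25·19.5² + 0.15·49.5² = 714.75.
- Within-site variance of change: 0.60·(1.5² + 1) + 0.25·(3.5² + 1) + 0.15·(5² + 1) = 9.16.
- Between-site variance of change: 0.06²·714.75 = 2.57 (control) and 0.10²·714.75 = 7.15 (treated), average 4.86.
- Unadjusted: SD = √(9.16 + 4.86) = 3.74, standardized effect 2.02/3.74 = 0.54, power Φ(0.54·√41 − 1.96) ≈ 0.93.
- Adjusted for site: the between-site part falls to 0.02²·714.75 = 0.29, because one common treatment effect is fitted. SD = √9.45 = 3.07, effect 0.66, power ≈ 0.99.

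The large joints, 15% of patients, supply 15/50.5 = 30% of the mean change. They supply 46% of the treated-arm variance (42-48% over the measurement errors of 0.5-2 mm and shrinkage SDs of 5-8% tried).

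If every joint loses the same number of millimetres, the between-site term is zero. Adjustment then changes almost nothing.

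**3. Simulated power (all inputs assumed).** 82 per arm, one joint per patient, joints of 25/70/115 mm in a 50/30/20% mix, swelling 50% v 65% resolved (SD 30 points), two-sided 5%, no Bonferroni. Ranges cover reading error of 1% of joint size and a fixed 1 mm.

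| Analysis of mm change | Swelling scales with size (15/12/10%) | Same mm at every joint (about 6 mm) |
|---|---|---|
| t test | 44-50% | 61-66% |
| Rank test | 46-56% | close to the t test |
| Adjusted for baseline dimension and site | 61-67% | 62-67% |

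A repeat run with a different random seed agreed to within about three points, and type I error without a treatment effect stayed near 5%.

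**4. Changing the scale instead.** The log ratio of day 7 to baseline, without a site term, reaches about 72% when swelling scales with size and reading error is proportional. With a fixed 1 mm error it reaches 53%. If swelling is the same in millimetres at every joint, it falls to 47% against 66% for the plain t test. Adding joint site brings this back to 65% when reading error is proportional to size, but not fully when the error is a fixed number of millimetres.

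**The case against.** The strongest reply is that the size of the problem is assumed. The article gives no joint sizes, no mix of sites and no caliper SD, and names no toe, ankle or knee. That stands: every power figure is an illustration. With other inputs the gain from rescaling vanishes. At swelling of 20/10/7% of size, power is 63% for the t test, 66% for the rank test and 61% for the log ratio.

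Second, the plan moves to a rank test when normality fails, and with such a mixture it usually would. This recovers part of the loss: 38% to 47% in a run with 12.5% swelling at every joint. The table therefore shows the rank test, and the adjusted analysis remains ahead when swelling scales with size.

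Third, scaling and covariates are often left to an analysis plan. That is fair for how several joints in one patient are combined, which is not counted here. But the article itself states both the measure and the test, and that test has no adjustment.

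A reader might also infer that the comparison is biased because it depends on how many large joints fall in each arm. It is not. Taking change from baseline removes the difference in absolute size, and randomization balances the mix in expectation. What remains is chance imbalance, which costs precision.

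**Conclusion.** The point holds as one of precision and interpretability. As stated, the caliper co-primary is a plain change at any joint site, tested without adjustment. If swelling loss scales with joint size, adjustment for baseline dimension and site raises illustrative power from 44-50% (t test) or 46-56% (rank test) to 61-67%. If it does not, nothing is lost (61-66% v 62-67%). These figures assume one joint per patient, the 50/30/20 mix and the other inputs listed. A Bonferroni-reduced alpha would lower them all.

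Two stronger readings are tempting, and the documents support neither. The first is that large joints dominate the mean. With an 80/15/5% mix of 30/70/100 mm joints, small joints still supply 0.80·30/39.5 = 61% of it. The second is that the result has no clinical meaning. The direction of change is clear, and the 0-10 swelling VAS, also a primary outcome, does not depend on joint size.

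**What to change.** In Statistical analysis, replace the unadjusted test for caliper change with a linear model (ANCOVA) containing treatment, the joint's baseline dimension and joint site. Use robust standard errors if the residual spread grows with joint size. Report millimetre change by joint site as description. Percent change or log(day 7/baseline), with joint site as a factor, may be added as a supportive analysis. It should not replace millimetres as primary, because it can lose power if swelling does not scale with joint size.

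The cost is a change of wording: same calipers, readings and visits. Baseline dimension is already recorded. Each joint has to be identified for its readings to be repeated, but the article lists no separate field for site, so confirm that the case report form names it. Settle the change before unblinding, so that the choice of model is not driven by the data.
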